### Participants

#### Overview

In total, 120 German- or French-speaking children and adolescents aged 8 to 16 years will be included in the study. In each subgroup (cancer, ADHD, and healthy controls), 40 (33.3%) participants will be randomly allocated to either the Mio-Training (n=20) or the waiting control group (n=20), with age (8 to <12 years vs 12 to 16 years) and sex (male vs female) as stratification factors (1:1 allocation ratio). The randomization sequence will be generated by an independent statistician and implemented in REDCap (Research Electronic Data Capture; Vanderbilt University) to ensure concealment of allocation. Randomization will be performed at the study site (Children’s University Hospital Bern).

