#### Primary Outcome

The primary end point will be the change score in metacognitive abilities, as measured by the Jr.MAI [47] calculated based on the change between baseline and the 3-month follow-up assessment. The score summarizes 18 items and evaluates metacognitive abilities, focusing on metacognitive knowledge and regulation. The score ranges between 18 and 90, with higher values indicating better metacognitive abilities. Research findings confirmed the validity of the Jr.MAI and demonstrated the reliability of the overall score with a Cronbach α of 0.87 [52]. The Jr.MAI will be assessed in all subgroups and both experimental groups (Mio-Training vs waiting control) before and after the training and waiting period and at 3-month follow-up.

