Statistical analyses will be conducted using RStudio (Posit PBC). The planned statistical analyses were developed in consultation with an experienced statistician. The level of significance is set at α=.05. Data will be tested for normal distribution. The primary analysis will follow an intention-to-treat approach using linear mixed-effects models to calculate 2-sided 95% CIs for the primary outcome (Jr.MAI total score). The mixed-effects model will contain the total score of the Jr.MAI, the time points (ie, baseline, 5-week follow-up, or 3-month follow-up, as a categorical variable), treatment allocation (ie, Mio-Training vs waiting control group), the baseline score of the Jr.MAI (to adjust for individual differences in baseline functioning and to improve statistical precision), and stratification factors as fixed effects. The primary effect of interest is the treatment allocation-by-time point interaction. Participant ID will be included as a random intercept. Secondary end points will be analyzed using the same method. A per-protocol analysis will be conducted as a sensitivity analysis using the same model structure restricted to adherent participants (≥80% intervention compliance). Additional sensitivity analyses will examine differences in slopes over time between groups. Subgroup analyses will investigate potential effect modification by sex and age via interaction terms (treatment×sex and treatment×age), with stratified results reported where appropriate. Missing data exceeding 5% will be handled using multiple imputation by chained equations (50 datasets), incorporating all baseline and outcome variables at all time points as predictors. Rubin’s rules [64] will be used for pooling estimates. Variables with more than 50% missing values will not be used for the imputation model. To address multiplicity arising from secondary and subgroup analyses, a false discovery rate correction will be applied where appropriate. The primary analysis will not be adjusted for multiplicity, as it is prespecified and confirmatory. Secondary and exploratory subgroup analyses (including sex and age interactions) will be interpreted with false discovery rate–adjusted *P* values to control for type I error inflation arising from multiple comparisons.

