Integrating metacognitive abilities into cognitive training is a critical factor in enhancing training efficacy, particularly in pediatric populations where introspection, self-reflection, and thinking about cognitive self-optimization are still absent or only emerging [35-41,68]. Metacognitive abilities—such as reflecting on one’s own thinking, learning and mnemonic strategies, and task performance—promote self-regulated learning and deeper cognitive engagement. Research has shown that metacognitive abilities (ie, planning, monitoring, and evaluating one’s own cognitive processes) are strongly associated with academic achievement, problem-solving abilities, and long-term school outcomes [69]. In children, especially those with atypical development, metacognitive abilities can encourage active participation in their learning, which can enhance motivation, persistence, and self-efficacy and, through this, support the transfer of trained skills (ie, the application of mnemonic strategies) to school and everyday life [35-41,68]. Thus, metacognitive abilities do not merely supplement cognitive training but rather enhance its relevance and long-term efficacy. Strong metacognitive abilities can give individuals a sense of agency over their rehabilitation journey [40].

Increasing evidence from developmental neuroscience suggests that motor coordination and cognitive functions, particularly executive functions and working memory, share overlapping neural networks, including the cerebellum, prefrontal cortex, and parietal regions [70,71]. Coordinative motor activities require goal-directed behavior, inhibition, and attentional control—all core components of executive functioning. Incorporating motor coordination exercises into cognitive training can therefore support the development of higher-order cognitive skills. Coordination tasks can thus enhance cognitive processes through embodied learning mechanisms [72]. Moreover, coordination tasks are often of a playful nature and hence increase motivation, engagement, and the experience of self-efficacy. The multimodal stimulation may be particularly beneficial for children and adolescents with atypical development [73], such as those with ADHD or pediatric cancer, whose neural systems may require multisensory and integrative stimulation to strengthen cognitive, everyday, and school performance.

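### Age band and sex enter the primary model only as main effects, so they cancel from the treatment-by-time contrast and the primary test does not account for the stratified randomisation

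*Protocol article*

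**What the plan says.** All of this comes from the protocol article.

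- **Randomisation** (Participants, Overview): 1:1 within each population of 40, "with age (8 to <12 years vs 12 to 16 years) and sex (male vs female) as stratification factors (1:1 allocation ratio").
- **Primary endpoint** (Primary Outcome): a Jr.MAI change score, "calculated based on the change between baseline and the 3-month follow-up assessment".
- **Outcome visits in the model** (Statistical Analysis): "the time points (ie, baseline, 5-week follow-up, or 3-month follow-up, as a categorical variable"). Baseline is a level of time, so the baseline score is part of the response.
- **Baseline score as covariate** (same section): it is also a fixed effect, "to adjust for individual differences in baseline functioning and to improve statistical precision".
- **Strata and primary effect** (same section): "stratification factors as fixed effects. The primary effect of interest is the treatment allocation-by-time point interaction".
- **Covariance** (same section): "Participant ID will be included as a random intercept".

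Age and sex interactions are written out only for the subgroup analyses, as treatment-by-sex and treatment-by-age. No age-by-time or sex-by-time term is named. Secondary endpoints use the same method.

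**The concern.** The primary effect is a contrast within the child: change from baseline to 3 months, compared between arms. A main effect of age band or sex raises or lowers every visit of a child by the same amount, so it cannot alter that contrast. The text reads as if the analysis adjusts for the stratification factors, but for the primary effect it does not.

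The stake is precision. If the two age bands change at different rates, that variation stays in the residual although allocation was balanced on it. Under equal correlation, the standard error is then larger than the true one and the test runs below its nominal 5%. The Discussion makes some age-related change plausible, since it describes children in whom "introspection, self-reflection, and thinking about cognitive self-optimization are still absent or only emerging". Each population has only 40 children, and the same model serves every secondary endpoint.

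**Working it through.** **Inputs.** From the article: 40 children per population (20 per arm), three visits, retest correlation 0.5, two-sided alpha 0.05, random intercept. Assumed, because the article gives no figure: balanced strata, complete data, and a difference δ (in SD units) between age bands in change from baseline to 3 months. The 5-week difference is taken as half of δ or equal to it. No sex effect on change is assumed.

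**1. The plan's own figure.** G*Power within-between interaction with f = 0.25, N = 28, m = 3 visits, ρ = 0.5: λ = f²Nm/(1−ρ) = 0.0625 × 28 × 3 / 0.5 = 10.5, with 2 and 52 degrees of freedom. Power is 0.812, so the stated 28 per population is reproduced. It rests on three visits and an equal correlation of 0.5, the setting used in steps 3 and 4.

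**2. Cancellation.** Write Y_ij = μ_j + τ_j·T_i + γ·z_i + b_i + e_ij, with z_i the strata. In Y_i3 − Y_i1 both γ·z_i and b_i vanish. The estimate is the difference between arms in mean change. Its standard error comes from the within-child residual on 2 × (40 − 2) = 76 degrees of freedom. Random-intercept fits to one simulated data set of 40 children confirm this:

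| Fixed effects beyond treatment-by-time | Estimate at 3 months | SE |
|---|---|---|
| none | 0.8115 | 0.2982 |
| age, sex | 0.8115 | 0.2982 |
| baseline, age, sex | 0.8115 | 0.2982 |
| baseline, age-by-time, sex-by-time | 0.7733 | 0.2970 |

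**3. Size under equal correlation.** The within-child variance is 1 − 0.5 = 0.5. Leaving out age-by-time adds (40/4)·δ²·S/76, where S is the centred sum of squares of the age profile over visits: (0, ½, 1) gives S = 0.5 and (0, 1, 1) gives S = 0.667. Example for δ = 1 and S = 0.667: 0.5 + 10 × 0.667/76 = 0.588, and √(0.588/0.5) = 1.084. The critical values, 1.992 on 76 df and 1.993 on 72 df with the four extra terms, hardly matter.

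| δ | Residual variance | CI wider than with by-time terms | Type I error |
|---|---|---|---|
| 0.5 SD | 0.516–0.522 | 1.5–2.1% | 4.5–4.7% |
| 0.67 SD | 0.530–0.539 | 2.8–3.8% | 4.2–4.4% |
| 1 SD | 0.566–0.588 | 6.3–8.3% | 3.4–3.7% |

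Simulations of the three-visit model agree: about 2%, 3–4% and 6–8%, with type I error of 4.3–4.8%, 4.2–4.5% and 3.2–3.7%. At δ = 0.25 SD the widening is 0.2% in simulation. At δ = 1 SD, an effect with about 80% power when the by-time terms are included has about 76% as written.

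**4. Cost when age does not matter.** Simulated CI half-widths are 0.626 SD as written and 0.628 SD with the by-time terms.

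**5. If correlation decays.** Take 0.6 between adjacent visits and 0.36 from baseline to 3 months. A random intercept imposes the average correlation, (0.6 + 0.6 + 0.36)/3 = 0.52. The model then gives change a variance of 2(1 − 0.52) = 0.96, against a true 2(1 − 0.36) = 1.28. The SE ratio is √(0.96/1.28) = 0.866, which gives a type I error of about 8.9% with no age effect. In simulation, coverage at δ = 0.5 SD is 91.4% as written and 91.0% once by-time terms are added. At δ = 1 SD it is 93.3% and 91.2%.

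**The case against.** **The harm is conditional and small.** A full 1 SD difference between age bands in change over about 17 weeks is a lot to assume. The Discussion says metacognition is emerging in children, but it does not compare change below and above age 12. At 0.25 to 0.5 SD the loss is about 0.2% to 2% of CI width. This stands, and it sets the weight of the point.

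**A reader might infer larger losses from a change-score formula.** The ratio 1/√(1 − R²) gives 11.8% for δ = 1 SD (R² = 0.25/1.25 = 0.20). That formula belongs to an analysis of a single change score. The planned model pools its residual over three visits, which brings the loss down to 6–8%.

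**A reader might infer that the interval is certainly too wide whenever age predicts change.** The plan does not support that. Under decaying correlation the random-intercept structure makes the interval too narrow, and this can outweigh the effect of the strata. Adding by-time terms alone then lowers coverage a little further. So the covariance has to be part of the repair.

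**The article is condensed, and a fuller plan may name the terms.** This has some force. But the article lists the fixed effects one by one and writes out age and sex interactions where it wants them, in the subgroup analyses. Main effects are the natural reading. Those subgroup terms do not remove age-related change from the primary contrast.

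**The cause is wider than the strata.** Baseline is both outcome and covariate, so the baseline covariate cancels in the same way, against its stated purpose. This is correct, and the preferred repair deals with both.

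**Conclusion.** The point holds as a matter of precision. With complete or fully imputed data and a positive estimated intercept variance, age band and sex have no influence on the primary contrast or its standard error, so the primary test does not account for the stratified randomisation. When the intercept variance is estimated at zero (12–30% of the equal-correlation simulations), the main effects change the SE slightly.

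If age predicts change, and visits are equally correlated at 0.5 with 20 children per arm, the CI is wider by about 2%, 3–4% and 6–8% for age effects of 0.5, 0.67 and 1 SD. Type I error is then about 4.3–4.8%, 4.2–4.5% and 3.2–3.7%. The article gives no figure for how age or sex predicts change, so which row applies is unknown. With decaying correlation the interval can be too narrow instead.

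A reader might also infer a biased treatment estimate. Nothing here supports that: allocation is randomised and balanced on the strata, and what is lost is precision.

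**What to change.** Preferred: use only the 5-week and 3-month Jr.MAI scores as outcomes, with baseline Jr.MAI, age band and sex as covariates, each by time. All three then act on the treatment contrast. The primary effect must be restated as the treatment difference at 3 months, because in this model the treatment-by-time interaction would only compare the 3-month effect with the 5-week effect.

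Alternative: keep all three visits, add age band-by-time and sex-by-time, and replace the random-intercept-only structure with an unstructured covariance. The by-time terms should not be added without the covariance change.

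Make the same change for the secondary endpoints. The Results section says that data analyses have not yet commenced, so this can still be fixed in advance. The cost is a short edit and a few degrees of freedom: for the by-time terms four, leaving 72 of 76 within-child degrees of freedom. There is essentially no widening if the strata do not predict change.

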On the basis of the background above, we developed the Mio-Training, an easily accessible, playful, multicomponent digital intervention that stimulates metacognitive abilities through the combination of motor coordination and cognitive training in a serious game. We evaluate the efficacy of the Mio-Training in a randomized controlled trial (RCT) in 3 groups of children and adolescents, namely children and adolescents with cancer, children and adolescents with ADHD, and healthy controls. We include healthy children and adolescents to evaluate the feasibility of the Mio-Training and to compare their data with those of the children and adolescents with cancer and ADHD.

The primary objective of this study is to investigate the short- and long-term efficacy of the Mio-Training on metacognitive abilities assessed with the Junior Metacognitive Awareness Inventory (Jr.MAI; primary outcome) [47]. Furthermore, we will investigate the efficacy of the Mio-Training on executive functions, processing speed, and memory (secondary outcomes). Additionally, the feasibility of the Mio-Training will be assessed (ie, usability, enjoyment, level of autonomy, and perceived impact).

We hypothesize that 5 weeks of Mio-Training will lead to improved metacognitive abilities in the short and long term (primary outcome) in children and adolescents with cancer and ADHD. Furthermore, an increase in metacognitive abilities will be associated with an increase in objective performance in executive functions, processing speed, and memory in the short term and with an increase in subjective performance in executive functions in the long term (secondary outcomes). In addition, we hypothesize that the Mio-Training will be perceived as feasible by the healthy children and adolescents and the patients with cancer and ADHD.

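### The declared primary end point is the T1-to-T3 change in Jr.MAI, but the primary test, and the sample size, use a three-visit interaction that does not isolate it

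*Protocol article*

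**What the plan says.** The protocol article describes the primary question in three ways.

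- **Methods, Primary Outcome:** the end point is a Jr.MAI change score, "calculated based on the change between baseline and the 3-month follow-up assessment". This is one contrast, T1 to T3.
- **Methods, Statistical Analysis:** the mixed model includes "the time points (ie, baseline, 5-week follow-up, or 3-month follow-up, as a categorical variable"), and "The primary effect of interest is the treatment allocation-by-time point interaction". No visit is singled out.
- **Introduction:** the objective is to "investigate the short- and long-term efficacy of the Mio-Training on metacognitive abilities", and the hypothesis for the cancer and ADHD groups is that training "will lead to improved metacognitive abilities in the short and long term (primary outcome"). Here T2 and T3 share primary status.

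On multiplicity, the Statistical Analysis section says: "The primary analysis will not be adjusted for multiplicity, as it is prespecified and confirmatory". False discovery rate control is kept for secondary and subgroup analyses.

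**The concern.** A two-arm interaction with a three-level time factor has two components, the treatment difference in T1-to-T2 change and in T1-to-T3 change. The omnibus test asks whether either differs from zero. The declared end point asks only about the second. The test that decides success can therefore be positive while the declared end point is null.

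The pattern that exposes this is a realistic one. The Introduction itself says that existing cognitive trainings improve the trained function straight after training but lack long-term effects. Durability is what the new training is meant to add, and the named test cannot tell a durable effect from one that has faded by 3 months.

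**Working it through.** **Inputs (Methods, Statistical Analysis and Participants):** repeated measures ANOVA, within-between interaction; effect size 0.25; α = 0.05; power 0.8; retest correlation ρ = 0.5; two arms; minimum 14 per arm (28 per subgroup); planned 20 per arm (40 per subgroup). The number of measurements m is not stated. The effect size is labelled f², but the stated sample size matches only if it is read as f = 0.25; f² = 0.25 taken literally gives N = 10 with m = 3.

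**1. Reproducing the plan's own figure.** For k = 2 arms, λ = f²·N·m/(1−ρ), df1 = (k−1)(m−1), df2 = (N−k)(m−1).
- m = 3, N = 28: λ = 0.0625 × 28 × 3 / 0.5 = 10.5 on 2 and 52 df; power 0.812. This is the smallest N that reaches 0.8, an exact match.
- m = 2 needs N = 34 and m = 4 needs N = 24. Neither matches.

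The trial was therefore sized on the three-visit, 2-df interaction.

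**2. What that test responds to.** Assume unit SD, compound symmetry with ρ = 0.5, no baseline covariate, and n per arm. The noncentrality is λ = (n/2)·SS/(1−ρ), where SS is the sum of squares of the between-arm differences at T1, T2 and T3 about their mean.
- T2-only pattern (0, d, 0): SS = d²(1/9 + 4/9 + 1/9) = (2/3)d².
- Sustained pattern (0, d, d): SS = d²(4/9 + 1/9 + 1/9) = (2/3)d².

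The two are identical, so power is identical. For n = 20, λ = 20·d²/(3 × 0.5) = 13.33·d².

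| Assumed T2-only effect (SD) | λ at 20 per arm | P(interaction significant), 20 per arm | 14 per arm |
|---|---|---|---|
| 0.5 | 3.33 | 34% | 24% |
| 0.8 | 8.53 | 73% | 56% |
| 1.0 | 13.33 | 90% | 76% |

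In 200,000 simulated trials with d = 0.8 and 20 per arm, the T1-to-T3 contrast was significant in 4.9%. The interaction was significant with a non-significant T3 contrast in 68%.

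The plan's own effect size points the same way. With m = 3, f² = SS/(4m), so f = 0.25 gives d² = 0.0625 × 12 / (2/3) = 1.125 and d = 1.06 SD for either pattern. The design power of 0.81 at N = 28 (0.94 at N = 40) thus applies equally to a training whose effect is gone by T3.

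**3. Type I error.** With no effect at any visit, the 2-df test rejected in 4.9% of simulated trials at 20 per arm. If the T2 and T3 coefficients (correlation 0.5 under these assumptions) were instead each tested at 0.05 and either counted, the rate was 9.0%. Under independence it would be 1 − 0.95² = 9.75%.

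**4. Sample size for the declared end point.** With m = 2, f = 0.25 and ρ = 0.5:
- N = 28: λ = 7.0, power 0.72
- N = 34: λ = 8.5, power 0.81
- N = 40: λ = 10.0, power 0.87

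This holds f fixed, which is 1.00 SD with two visits against 1.06 SD with three. Holding 1.06 SD fixed instead gives 15 per arm (N = 30). The loss allowance at 40 is 12/40 = 30% for N = 28 and 6/40 = 15% for N = 34.

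**The case against.** The best defence is that the sections can be read together as one contrast. The end point is fixed at T3, the model is said to yield confidence intervals for the primary outcome (which suits a 1-df estimate, not a 2-df test), and with T1 as reference the treatment-by-T3 coefficient is exactly the between-arm difference in T1-to-T3 change. Naming that coefficient could be left to an analysis plan that is not shown. This reading is possible, but the article names the whole interaction as the primary effect, and its sample size reproduces only for three visits. That is a conflict in what is stated, not a missing detail.

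Three stronger readings are tempting, and the documents do not support them.

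- **That the unadjusted primary analysis inflates the type I error.** For one omnibus test it does not. The figure of about 9% needs a rule that either visit counts, which the plan nowhere states. The hypothesis says short and long term, and requiring both would need no adjustment.
- **That the error compounds to about 17% over ADHD and cancer** (1 − (1 − 0.0907)²). The two studies have separate ethics approvals and registrations, and the ADHD study will be analyzed and published first. They are best treated as separate claims.
- **That the 34% to 90% are false-positive rates, or that a long-term claim would go through unchecked.** A T2-only effect is a real effect and falls within the Introduction's objective. The planned model would also give a T3 estimate and interval that show its absence. The percentages show only that a significant primary test does not speak to the declared end point.

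**Conclusion.** The point holds as a mismatch between end point, test and hypothesis. The primary test and the sample size belong to a three-visit interaction, while the declared end point is the T1-to-T3 change. The mismatch and the three-visit origin of N = 28 follow from the article's own text and inputs, with its effect size read as f.

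The 34%, 73% and 90% rest on assumed effects of 0.5, 0.8 and 1.0 SD, compound symmetry with ρ = 0.5, 20 complete participants per arm and no baseline covariate. Multiplicity is a conditional side issue: about 9% per population, and only if T2 and T3 are each tested and either counts.

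It should be settled now. The Results section says that analyses have not begun, but 39 of 40 ADHD participants are recruited and that study reports first.

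**What to change.** In the Statistical Analysis section, name the 1-df treatment difference in T1-to-T3 change (the treatment-by-T3 contrast, T1 as reference) as the single confirmatory test in each clinical population, ADHD and cancer. Make the omnibus interaction secondary. Make the T2 difference secondary, or test it after T3 in fixed order. Change the Introduction so that the objective and hypothesis give T2 and T3 these same roles. The statement on multiplicity can then rest on there being one primary contrast per population, not on prespecification.

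Restate the sample size for this contrast, with the number of measurements given: 34 per subgroup under the article's own inputs (power 0.81), with 0.87 at 40 if nobody is lost.

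The cost is mostly wording, and the planned 40 per subgroup can stay. T2 loses co-primary status, and the loss allowance at 40 falls from 30% to 15%, so retention to T3 matters more than the present text suggests.

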## Methods

### Design and Setting of the Study

The study is an investigator-initiated RCT including 2 experimental groups (Mio-Training and a waiting control group). We will investigate the efficacy of the Mio-Training using the same study design in three subgroups, namely (1) healthy children and adolescents, (2) children and adolescents with cancer, and (3) children and adolescents with ADHD.

Participants will be screened for eligibility according to the inclusion and exclusion criteria by a study investigator (for details, see participants section [cancer survivors, children and adolescents with ADHD and healthy controls]). After the screening, 3 study visits will take place at the Division of Neuropediatrics, Development and Rehabilitation at the Inselspital in Bern or at the participants’ home. Cognitive and motor assessments will be performed before the intervention and the waiting period (baseline assessment; T1) and will be repeated after 5 weeks at immediate follow-up (T2). The questionnaires will be completed again at a 3-month follow-up (T3; Figure 1).

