**Figure 1. F1:**
[figure not shown]
Study flow chart. T0: screening; T1: first assessment (before intervention or waiting period); T2: second assessment (immediately after intervention or waiting period); T3: third assessment (12 weeks after intervention or waiting period).

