### Statistical Analysis

The sample size was calculated for the primary outcome measure (Jr.MAI total score) using G*Power 3: repeated measures ANOVA (within-between subjects interaction); small effect size (Cohen *f*^2^=0.25); α=.05, power=0.8; retest correlation=0.5. The resulting minimal sample size is 14 participants per experimental group (Mio-Training vs waiting control group), corresponding to n=28 per subgroup (healthy controls, children and adolescents with cancer, and children and adolescents with ADHD). To compensate for losses and dropouts, the sample size was defined as 40 participants per subgroup, with a total sample size across all 3 subgroups of 120.

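### The primary model names only a random intercept, which by default assumes one correlation for all pairs of visits at weeks 0, 5 and 17; if baseline to T3 is the weakest pair, the interval for the primary contrast is too narrow

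*Protocol article*

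**What the plan says.** All references are to the protocol article.

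- **Model (Statistical Analysis).** The Jr.MAI total score is analysed by a linear mixed-effects model with fixed effects for "the time points (ie, baseline, 5-week follow-up, or 3-month follow-up, as a categorical variable", for treatment allocation, for "the baseline score of the Jr.MAI (to adjust for individual differences in baseline functioning and to improve statistical precision", and for the stratification factors. On the within-child structure the section says: "Participant ID will be included as a random intercept". It names no other random effect, residual correlation, visit-specific variance or robust standard error.
- **Effect tested (same section).** "The primary effect of interest is the treatment allocation-by-time point interaction".
- **Endpoint (Primary Outcome).** The change score is "calculated based on the change between baseline and the 3-month follow-up assessment".
- **Timing.** Assessments "will be repeated after 5 weeks at immediate follow-up (T2" (Design and Setting of the Study). The Figure 1 legend gives "T3: third assessment (12 weeks after intervention or waiting period".
- **Sample size (Statistical Analysis).** One correlation is given: "retest correlation=0.5".

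Secondary endpoints and the per-protocol analysis reuse the same model.

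**The concern.** A random intercept with independent, equal-variance residuals is compound symmetry: one variance, and one correlation for every pair of visits. The three gaps here are 5 weeks (T1-T2), 12 weeks (T2-T3) and 5 + 12 = 17 weeks (T1-T3). Repeated questionnaire scores may well agree more closely over 5 weeks than over 17. The model would then average the three correlations and apply the average to the pair that defines the primary endpoint.

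With complete data the estimated T1-T3 treatment effect does not change. What changes is its standard error, and with it the 95% interval and any p value attached to that contrast. Nothing else in the plan corrects this. The slope sensitivity analysis looks at group differences in slope and leaves the primary interval as it is.

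**Working it through.** **1. The plan's own figure.** For the within-between interaction, use a noncentral F with lambda = f² × N × m / (1 − r), df1 = m − 1 and df2 = (N − 2)(m − 1). With f = 0.25, m = 3 visits, r = 0.5 and N = 28, lambda = 0.0625 × 28 × 3 / 0.5 = 10.5 and power is 0.812. The stated 28 per subgroup is reproduced when 0.25 is entered as f. So the sample size also rests on one correlation for all three visits.

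**2. Standard error of the T1-T3 contrast.** Let the score variance be σ² at each visit.

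- True variance of one child's T1-T3 change: 2σ²(1 − r13).
- Variance that the random-intercept model uses: 2σ²(1 − r̄), where r̄ is the mean of the three correlations.
- True SE / model SE = sqrt[(1 − r13)/(1 − r̄)].
- Approximate type I error = 2 × [1 − Φ(1.96 × model SE / true SE)].

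Example, 0.7/0.7/0.5: r̄ = 0.633, so the ratio is sqrt(0.5/0.367) = 1.17. The interval is 1 − 1/1.17 = 14% too narrow, and the type I error is 2 × [1 − Φ(1.96 × 0.856)] = 9.3%.

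**3. Results.** The correlations are assumptions, since the article gives none by time gap. The simulations use 20 children per arm, complete data and no treatment effect.

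| T1-T2 / T2-T3 / T1-T3 | True SE / model SE | Interval | Type I error, formula | Type I error, simulated |
|---|---|---|---|---|
| 0.50 / 0.50 / 0.50 | 1.00 | correct | 5.0% | about 5% |
| 0.55 / 0.50 / 0.45 | 1.05 | 4.7% too narrow | 6.2% | 6.0% |
| 0.60 / 0.50 / 0.40 | 1.10 | 8.7% too narrow | 7.4% | 7.2% |
| 0.70 / 0.70 / 0.50 | 1.17 | 14.4% too narrow | 9.3% | 9.2% |
| 0.70 / 0.60 / 0.40 | 1.18 | 15.0% too narrow | 9.6% | 9.6% |
| 0.40 / 0.50 / 0.60 | 0.89 | 11.8% too wide | 2.8% | 2.9% |

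Separate simulation runs differ by a few tenths of a point.

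**4. The contrast with its own variance.** Testing the T1-T3 change with its own variance gives a simulated type I error of about 5% in every row.

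**5. The joint test.** The two-degree-of-freedom treatment-by-time test has a simulated type I error of 4.9% to 5.6% over these patterns.

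**6. Unequal variance alone.** Take correlation constant at 0.5 and variances of 1, 1.15 and 1.3.

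- Variance of the T1-T2 change: 2.15 − sqrt(1.15) = 1.078.
- Variance of the T2-T3 change: 2.45 − sqrt(1.495) = 1.227.
- Variance of the T1-T3 change: 2.30 − sqrt(1.3) = 1.160.
- Their mean is 1.155, so the ratio is sqrt(1.160/1.155) = 1.00. There is practically no effect.

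**7. Baseline as covariate only, T2 and T3 as outcomes, random intercept kept.** The model forces one residual variance on both visits. Model SE / true SE at T3 = sqrt[mean(1 − r12², 1 − r13²)/(1 − r13²)]. For r12 = 0.7 and r13 = 0.5 this is sqrt(0.63/0.75) = 0.917, giving 7.2%. The problem is smaller than the 9.3% in step 2, but it remains.

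**The case against.** The strongest reply has three parts.

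- **Compound symmetry is inferred from what the article does not say.** A random intercept can be combined with a residual correlation structure or robust standard errors, and an article may leave these to a fuller plan. This stands. A reader might infer that the article commits the trial to equal correlations, but it names the random intercept and does not rule out more. The point therefore holds for the model as written, with default residuals.
- **The harm rests on assumed correlations.** This also stands. A reader might infer that the primary interval will be too narrow in all three populations. The documents do not support that. Their only correlation is a common 0.5, where the loss is zero, and the reverse pattern makes the interval too wide. Nothing in the article shows that T3 is less well predicted by baseline than T2 is.
- **The named effect is the interaction, and its joint test is hardly affected.** This is correct for the joint test. A reader might infer that the confirmatory p value is inflated whichever test is used, and step 5 shows otherwise. But the Primary Outcome section makes baseline to T3 the endpoint, and an interval has to be attached to a single contrast. The concern survives for that contrast and its interval.

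The absence of a multiplicity adjustment for the primary analysis is a separate matter and adds no weight here.

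**Conclusion.** The point holds as a conditional weakness with an inexpensive remedy. The documents do not show that an error will occur.

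If T1-T3 is the weakest of the three correlations, and the model is fitted with default residuals to complete data from 20 children per arm, the interval for the T1-T3 contrast is about 5% to 15% too narrow and its type I error is about 6% to 10%. At equal correlation there is no loss. If T1-T3 is the strongest pair, the interval is conservative. The driver is unequal correlation; moderately unequal variance has little effect alone. The direction under falling correlation is certain, but the size depends on correlations that the article does not give.

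**What to change.** **Change.** In Statistical Analysis, replace the random intercept with an unstructured within-child covariance over the visits analysed as outcomes (in R, the mmrm package, or nlme::gls with a general correlation and visit-specific variances). Use Kenward-Roger or Satterthwaite degrees of freedom. Name the treatment contrast at T3 as the primary estimate, with baseline-adjusted ANCOVA at T3 as the fallback if the model does not converge. Use the same structure for secondary outcomes measured at all three visits, such as the BRIEF. Outcomes measured only at T1 and T2 have a single pair of visits, so the equal-correlation assumption does not arise.

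**A practical condition.** Give baseline one role, either an outcome row or a covariate. With both, a coefficient of 1 on the covariate would fit the baseline row exactly and let its variance shrink to zero, so an unstructured model could not be fitted sensibly.

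**Cost.** One line of specification, with six covariance parameters for three outcome visits or three for two, which 40 children per subgroup can support. If correlation is in fact constant, the interval widens slightly. Ignoring covariates, residual degrees of freedom fall from 2 × (40 − 2) = 76 to 38, and the t multiplier rises from 1.992 to 2.024, about 1.6%. The article reports that analyses have not begun, so the change can still be prespecified before the ADHD results.
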